### *3.9.2 Serious Adverse Events*

Any adverse experience occurring at any dose that results in any of the following outcomes:

- **Death**
- **Life threatening**- defined as an experience that places the patient or subject, in the view of the Investigator, at immediate risk of death from the reaction as it occurred. (Note: this does not include a reaction that, had it occurred in a more severe form, might have caused death).
- Requires inpatient **hospitalisation** or prolongation of existing hospitalisation.
- Results in a **congenital** anomaly or birth defect.
- Results in a **persistent or significant disability** or incapacity.
- **Important medical events** that may not result in death, be life-threatening or require hospitalisation may be considered as a serious adverse drug experience when, based upon appropriate medical judgement, they jeopardise the patient or subject and may require medical or surgical intervention to prevent one of the outcomes listed above (for example, an event may be defined as serious based on a deterioration in grade in Toxicity Tables).

Any serious adverse event that occurs during the study period will be reported to the Local Safety Monitor and Chairman of DSMB.

# *3.10 Morbidity surveillance during the rainy season*

Passive surveillance for malaria will be maintained throughout the transmission season. Parents/guardians will be encouraged to take their child to the health centre identified as being closest to their home at any time that their child becomes unwell. Project staff will be based at each of these health facilities to identify children in the trial and to ensure that they are seen, properly investigated and treated promptly. At each clinic visit, axillary temperature will be recorded using a digital thermometer and haemoglobin concentration measured using a Hemocue machine. A dipstick for diagnosis of malaria will be used if fever (axillary temperature of  37.5°C) or a history of fever within the previous 48 hours is present. In such cases, a thick blood smear will also be collected for subsequent confirmation of the diagnosis. Study subjects with documented fever (axillary temperature of  37.5°C) or history of recent fever and malaria parasitaemia will be treated with Coartem. The treatment of study subjects seen at the health centres for other conditions will be the carried out in accordance with national guidelines.

# *3.11 End of malaria transmission season cross-sectional survey*

Children enrolled in the study will be seen at the OPD clinic at the end of malaria transmission season for examination by a study physician and a finger-prick blood sample will be obtained for preparation of a thick blood smear and determination of haemoglobin concentration. A standardized questionnaire will be administered to the parents/guardians of the study subject, to collect information regarding illness that had occurred since the last visit, symptoms experienced, use of healthcare facilities and use of medicines. Information on the use of bed nets will be collected again at this visit.

*3.12 Study end-points:*

*3.12.1 Primary end points*

*Safety endpoint*

- Incidence of any adverse events during the observation period.

*Secondary end points*

- Mean Hb (g/dl) at the end of malaria transmission.
- Prevalence of malaria parasitaemia at the end of the malaria transmission season.
- Number of OPD attendances with malaria that meet the case definitions as indicated below during the surveillance period.

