It is not certain whether IPTc could be effectively delivered through the infrastructure of the Reproductive and Child Health (RCH) service given the ever increasing workload of the RCH clinics. With support from the Gates Malaria Partnership, a study to compare two strategies for the delivery of intermittent preventive treatment in children was undertaken in 2006 in 14000 children in Upper River Division of The Gambia where malaria transmission is seasonal. Twenty-six RCH trekking clinics in Upper River Division were randomly allocated to receive IPT from the RCH trekking team or from a village health worker. Treatment with a single dose of sulfadoxine /pyrimethamine (SP) plus three doses of amodiaquine was given to all study subjects at monthly intervals on three occasions during the months of September, October and November. Preliminary analysis of the results showed that the treatment was very effective as only 4% (45/1133) of the children seen at the end of year cross-sectional survey were parasitaemic. Compliance was initially high but decreased progressively with increase in the number of doses taken by the study subjects. 81%, 74% and 67% of study subjects in the VHW arm received IPT during September, October and November respectively. In the RCH arm, 69%, 51% and 48% received IPT during September, October, and November respectively. Tolerability was assessed in a subset of 1100 children and the results showed that about 13.5% of children developed mild to moderate vomiting but there was no control group for comparison. Mild to moderate malaise was present in about 10% of the study subjects. Severe adverse event was rare. However, these adverse events had a negative impact on compliance because of the perception among the study population that the trial medication was associated with a significant number of adverse events. Thus, it is important to investigate if other drug combinations might be equally effective in preventing malaria but more effective in preventing adverse events. Thus, we now propose to compare the safety, efficacy and tolerability of three potential drugs combinations for IPTc. The drugs combinations that we have selected for comparison are amodiaquine plus sulfadoxine-pyrimethamine (the combination used in the previous study), sulfadoxine-pyrimethamine plus piperaquine (another long acting drug) and Artekin TM (dihydoartemsinin plus piperaquine).

*1.2.4 Potential drugs for use in IPT*

Amodiaquine

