# *3.9.1 Surveillance for adverse events*

An adverse event is defined as any unfavourable and unintended sign, symptom, syndrome, or illness that develops or worsens during the period of observation in the clinical study. Clinically relevant abnormal results of diagnostic procedures including abnormal laboratory findings (e.g., requiring unscheduled diagnostic procedures or treatment measures, or resulting in withdrawal from the study) which are considered by the Principal Investigator to be detrimental should be recorded as adverse events whether or not they have a causal relationship with the study drug. Where the laboratory result is a sign of another clinical condition, the clinical condition itself should be the reported adverse event. An event unequivocally caused by a significant deterioration of the underlying condition related to malaria is regarded as an adverse event.

To determine the prevalence of minor side effects following drug administration such as headache, fever, weakness, abdominal pain, anorexia, nausea, vomiting, diarrhoea, rash, itching or sleep disorder participants in each treatment group will be visited at home three and seven days after each round of drug administration and a side effects questionnaire completed. Field workers who complete these questionnaires will be unaware of the treatment group to which the child belongs. To help establish whether these adverse events are drug related, the same questionnaire will be administered once after each treatment round, to 286 children who are not part of the trial, recruited from nearby villages and matched for age to children in the trial.

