#### 3.13 Data management and analysis

All baseline, surveillance and laboratory data will be collected on forms designed for the trial. Field and laboratory staff will be trained to follow the procedures set out in a series of Standard Operating Procedures (SOPs). Key data will be double entered and inconsistencies checked; range checks will be used for standard variables. Primary analyses will be performed on an intention to treat (ITT) basis. Any child who receives a first dose of drug will be included in the ITT analysis. Children who are randomised but who do not receive any mediation will not be included in this analysis.

*3.14 Sample s-size calculations*

Drugs for IPT need to be acceptable and have low frequency of adverse events. If the frequency of adverse events is 20% in the SP/AQ group, a trial with 286 children per arm has 90% power to detect a halving in the frequency of adverse events, using a significance level of 0.05, or a reduction to 9% or less if a significance of 0.025 is used (to preserve an overall type 1 error rate of 5% for the primary endpoint when there are 2 comparisons, each alternative drug group with SP/AQ). If the frequency of adverse events is 15%, a reduction to 5% or less can be detected with the same power, and if the frequency is 10% a reduction to 2% or less can be detected. Based on experience from several studies the drop-out rate is not expected to exceed 15% and is likely to be less. Allowing for 15% drop out, a sample size of 286*3/(1-0.15)=1009 is needed.

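### The primary safety endpoint counts any illness from any cause, malaria included, so it mixes efficacy into safety and dilutes drug side effects by an amount that section 3.14 does not allow for

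*Protocol*

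**What the plan says.** Section 3.12.1 of the protocol gives the primary endpoint as "Incidence of any adverse events during the observation period". The observation period is not defined further.

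Section 3.9.1 defines an adverse event as "any unfavourable and unintended sign, symptom, syndrome, or illness that develops or worsens during the period of observation in the clinical study". No link to the drug is required. For clinically relevant abnormal results this is explicit: they "should be recorded as adverse events whether or not they have a causal relationship with the study drug". The same section adds: "An event unequivocally caused by a significant deterioration of the underlying condition related to malaria is regarded as an adverse event". Malaria is also counted among the secondary endpoints of 3.12: "Number of OPD attendances with malaria that meet the case definitions as indicated below during the surveillance period".

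Events can be picked up in several ways: a side-effects questionnaire with eleven named symptoms at home visits three and seven days after each of three rounds (3.9.1), passive clinic surveillance all season (3.10), and an illness questionnaire at the end-of-season survey (3.11).

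Section 3.14 states: "If the frequency of adverse events is 20% in the SP/AQ group, a trial with 286 children per arm has 90% power". The effect considered there is a fall by half, tested at significance level 0.05. At 0.025, used for the two comparisons with SP/AQ, it gives 9% or less as the detectable rate. It also gives 15% to 5% and 10% to 2%. It names no source, time window, counting unit (child or round) or background rate. The earlier Gambian figures in 1.2.3 are for single symptoms: "about 13.5% of children developed mild to moderate vomiting but there was no control group for comparison", and malaise in about 10%.

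**The concern.** The question is whether one combination causes fewer side effects than another. The endpoint as worded answers a wider one, namely which arm had less illness of any kind. That has two consequences.

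- **Efficacy enters the safety comparison.** A malaria attack is an illness that develops during observation, so an arm with weaker malaria protection collects more adverse events even if its drug is tolerated equally well. A difference reported as tolerability could be a difference in protection, and a real tolerability advantage could be offset by weaker protection.
- **Background illness dilutes the contrast.** Fever, diarrhoea and similar complaints occur in young children whatever drug they are given. A better tolerated drug can remove only the drug-caused part, so halving that part does not halve the endpoint.

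The protocol expects background events, since 3.9.1 adds 286 untreated children to help judge whether events are drug related. Section 3.14 makes no allowance for them.

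**Working it through.** **Inputs from the protocol.** 286 per arm; 20% v 10%; significance level 0.05, or 0.025 for two comparisons; 15% drop-out; three rounds. **Assumed, because the protocol gives no figure:** background risk b of 10%, 20%, 30% or 50% over the period, independent of drug effects; malaria risk of 5% v 15% in the example.

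**1. The plan's own figure.** Two-sided 0.05, pooled formula:

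n0 = [1.960 × √(2 × 0.15 × 0.85) + 1.282 × √(0.20 × 0.80 + 0.10 × 0.90)]² / 0.10² = 265.9.

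With continuity correction: n = (n0/4) × [1 + √(1 + 4/(n0 × 0.10))]² = 285.5, so 286. Total: 286 × 3 / 0.85 = 1009.4, stated as 1009. At 0.025 with the same correction, 20% v 9% needs 270, and 15% v 5% and 10% v 2% each need 241, so 286 is enough for all of them. The arithmetic of 3.14 stands.

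**2. Malaria inside the endpoint.** Any-event risk = 1 − (1 − drug-caused risk)(1 − malaria risk). With 20% drug-caused risk in both arms:

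- malaria 5%: 1 − 0.80 × 0.95 = 24%
- malaria 15%: 1 − 0.80 × 0.85 = 32%

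The chance of a significant result at 0.05 with 286 per arm is Φ{[0.08 × √286 − 1.960 × √(2 × 0.28 × 0.72)] / √(0.24 × 0.76 + 0.32 × 0.68)} = Φ(0.17) = 57%, with no difference in tolerability at all.

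**3. Dilution by background.** Any-event risk = 1 − (1 − b)(1 − d), where d is the drug-caused risk over the period. Two readings of 20% v 10%:

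- A: d applies to the whole period, 0.20 v 0.10.
- B: the risk recurs independently at each round, d = 1 − 0.80³ = 0.488 v 1 − 0.90³ = 0.271.

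Power is by the formula in step 2 (two-sided 0.05, no continuity correction, 286 per arm).

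| b | A: risks | A: power | B: risks | B: power |
|---|---|---|---|---|
| 0% | 20 v 10% | 92% | 48.8 v 27.1% | over 99.9% |
| 10% | 28 v 19% | 72% | 53.9 v 34.4% | 99.7% |
| 20% | 36 v 28% | 54% | 59.0 v 41.7% | 99% |
| 30% | 44 v 37% | 40% | 64.2 v 49.0% | 96% |
| 50% | 60 v 55% | 23% | 74.4 v 63.6% | 80% |

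The 92% in the first row is 90% with the continuity correction, as the protocol has it.

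**4. If 20% is already the all-cause total.** If a quarter or a half of it is background and the rest is halved, the risks are 20% v 12.5% (0.05 + 0.15/2) or 20% v 15% (0.10 + 0.10/2). Power is 68% or 35%.

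**5. Check on the cause.** A high event rate does not itself cost power: a halving of the whole endpoint from 30% to 15% would have 99%. The loss comes from events that the drug cannot change.

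**The case against.** The strongest reply is that 3.14 is a conditional statement about the total frequency of adverse events ("If the frequency of adverse events is 20% in the SP/AQ group") and makes no claim about a drug-caused part. That is right, and the figure reproduces. A reader might infer that the stated 90% power is false; the documents do not support that. What they show is that the assumed halving of an all-cause frequency is unexplained.

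A reader might also set power at 0.025 under reading A (62%, 42%, 30% and 15% for the four background rates) against the stated 90%. That comparison is unfair. At 0.025 the protocol claims 90% only for a fall to 9% or less, and 20% v 10% has 87% there even without background. Reading A is also only one possibility; reading B leaves power at 80% or more.

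The earlier 13.5% vomiting and 10% malaise do not contradict 20%. Together they cover 13.5% to 23.5% of children depending on overlap, and being uncontrolled they already include background. They do, however, concern only two symptoms.

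On malaria, the sentence about deterioration of an underlying condition fits poorly with children enrolled free of obvious health problems, and no malaria incidence under treatment is given. The general definition still admits malaria as an illness. The 24% v 32% is therefore an illustration of the mechanism and no estimate.

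The 286 untreated children show that background was considered. They do not cure the endpoint: they are not randomised, they are questioned once per round where trial children are visited twice, and they enter neither the endpoint nor the power.

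Finally, the observation period could be read as the post-dose visits only. The definition in 3.9.1 points to the whole study, and even the short windows contain some background illness.

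**Conclusion.** The concern holds for the endpoint definition. As written, the only primary endpoint counts illness regardless of cause, overlaps with a secondary efficacy endpoint, and can show a safety difference between equally tolerated drugs. This follows from 3.9.1 and 3.12 and needs no assumed rate; only its size does.

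On power, 286 per arm is correct for total frequencies of 20% v 10% at 0.05, so 90% holds if the whole any-event frequency halves. If only the drug-caused part halves, background lowers power at any given drug-caused risk, but the amount cannot be fixed from the protocol: over backgrounds of 10% to 50% it runs from 72% to 23% under reading A and from 99.7% to 80% under reading B. All of these rest on assumed background rates and independence. That the choice between per child and per round moves power this far is itself a reason to define the endpoint.

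**What to change.** - **Primary endpoint (3.12.1):** the proportion of children with at least one solicited symptom from the 3.9.1 list, made a closed list, starting between first dose and day 7 of any round.
- **Malaria:** count malaria attendances as efficacy. Report all other adverse events descriptively.
- **Sensitivity analysis:** show the primary result with and without symptoms belonging to confirmed malaria episodes. Do not make the exclusion primary, because it conditions on an outcome that arises after randomisation and depends on efficacy.
- **Sample size (3.14):** restate it for this per-child endpoint, say what the 20% refers to, and show power over a range of assumed background rates at both significance levels.

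**Cost:** protocol wording, and a questionnaire that records when each symptom began. The day 3 and day 7 visits are already planned, so no extra children or visits are needed. The downsides are that the stated power will probably be less favourable, and that some background symptoms will remain in the post-dose windows, so dilution is reduced but not removed.

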**Summary**

Intermittent preventive treatment (IPT) offers a potential way of preventing malaria infection without compromising the development of malaria immunity or encouraging drug resistance. The effect of IPT in children in the prevention of malaria has been evaluated in a number of trials in areas of seasonal malaria transmission. Results from these trials have shown that IPTc provided between 40% - 86% protection against clinical malaria. In 2006, a trial that compared two methods of IPTc delivery was carried out in Upper River Division, The Gambia. Preliminary results of the trial have shown that the treatment was very effective as only 4% (45/1133) of the children seen at the end of year cross-sectional survey were parasitaemic. Tolerability was assessed in a subset of 1100 children and the results showed that about 13.5% of children developed mild to moderate vomiting. Malaise was present in about 10% of the study subjects. Severe adverse events were rare. Thus it is important to investigate if other drug regimens might be equally effective in preventing malaria but less likely to cause adverse events. During the 2007 malaria transmission season, 1009 children aged 1-5 years will be individually randomized to receive amodiaquine plus SP, piperaquine plus SP or Artekin TM (dihdroartemisinin plus piperaquine) at monthly intervals on three occasions during the months of September, October, and November. To determine the prevalence of side effects following drug administration participants in each treatment group will be visited at home three and seven days after each round of drug administration and a side effects questionnaire completed. To help establish whether these adverse events are drug related, the same questionnaire will be administered after each treatment round, to 286 age-matched children who are not part of the trial. The primary ends points will be the incidence of adverse events.

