# *2.0 Objectives*

*2.1 Primary Objective*

To determine the safety and tolerability of AQ (three days) plus SP (one day), PQP (three days) plus SP (one day) and Artekin TM (PQP plus DHA) (3 days) when used for seasonal IPT in children.

*2.2 Secondary Objective*

To determine the efficacy of AQ (three days) plus SP (one day), PQP (three days) plus SP (one day) and Artekin TM (PQP plus DHA)(3 days) when used for seasonal IPT in children.

*3.0 Study design and methods*

*3.1 Study area*

The study will be based at the MRC Field Station in Basse in the Upper River Division (URD) of The Gambia. This is an area of savannah typical of much of sub-Sahelian Africa. Malaria transmission is seasonal, occurring mostly during the short rainy season (July - October), and is almost exclusively due to *P.* *falciparum*. *Anopheles gambiae* is the principal vector; the area has the highest entomological inoculation rate (EIR) in The Gambia (between 1 and 50 infective bites per person per year). The population has worked with the MRC for at least 20 years and cordial relations exist between the MRC and surrounding villages.

*3.2 Enumeration, recruitment and consent*

The study will be carried in collaboration with the National Malaria Control Programme and URD District Health Team and study children will be recruited from villages in the south bank of Upper River Division. During the preparatory phase of the study, the design and objectives of the study will be discussed extensively with the URD District Team and all health care providers working in the study area. The study team will visit all the villages in the study area to explain the objectives of the trial to village elders, opinion leaders and village health workers. This will be followed by village meetings, which the entire community will be invited to participate. During these meetings, agreement to participate in the study will be obtained from the villagers. In addition, parents or guardians of prospective study subjects in the right age group will be visited at home and they will be provided with flyers in English and the appropriate local language (Mandinka, Sarahule or Fula).

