Written informed consent will be obtained from the parent(s) or guardian(s) before a child is enrolled in the study. Approximately 1400 children aged between 1 to 5 years will be screened, of whom 1009 volunteers who meet the enrolment criteria will be enrolled in the study to receive SP plus AQ, SP plus PQP or Artekin TM. Clinic forms will be prepared and filled in by the study physician at screening. Each form will contain the subject’s initials, information about the subject’s date of birth, compound number, date of screening visit, whether the subject was enrolled or not and, when applicable, reasons for exclusion from the study based on medical history or physical or laboratory screening examination. A screening list will be prepared by the investigators as part of the routine source documentation. After review of the medical history, physical examination and laboratory results, reasons for non-eligibility will be documented on the list. Any clinically relevant finding will be treated at the discretion of the investigator. On entry into the trial a detailed clinical history, drug history, family history, and information on bednet usage and net impregnation will be obtained. The study physician will examine the child, document nutritional status and record the findings in a case report form. A finger-prick baseline blood sample will be obtained for determination of haemoglobin concentration and thick blood film preparation**.** Other investigations such as chest x-ray and urine examinations will be carried out as clinically indicated.

*3.3 Inclusion criteria*

1. Age between 1 to 5 years at enrolment.
2. Informed consent obtained from parents or legal guardians.
3. No current participation in another malaria intervention trial.
4. Free of obvious health problems as established by medical history and clinical examination before entering into the study.
5. Available for the duration of the study.

#

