***Withdrawal Criteria***

Study subjects may be withdrawn from the study for any one of the following reasons.

1. Withdrawal of parental / legal guardian’s consent.
2. Serious adverse event attributable to the study drug.
3. Loss to follow-up.

Children who develop adverse events attributable to study drugs should not receive further doses but should be followed-up to monitor safety up until the resolution of the adverse reaction.

*3.6 Randomisation*

Open-label, individual randomisation is proposed and will be done approximately three weeks before the first dose of IPTc administration planned for early September 2007. Study subjects will be individually randomised into either the AQ plus SP, PQP plus SP or ArtekinTM treatment groups in a 1:1:1 fashion. An independent statistician will generate the randomizing subject study number (SSN) that associates each SSN either to AQ plus SP, PQP plus SP or Artekin TM treatment groups and study subjects will be given treatment according to their randomisation group. A photo ID card will be given to all participants to facilitate identification at every contact, at home or in the health centres.

*3.7 Drug distribution at the health centres*

Study subjects and their parents will be informed about the date of treatment approximately one week before any intervention. Treatment will be given during the months of September, October and November. Drugs will be given at the nearest health centre by a designated member of staff. Tablets will be crushed, mixed with honey or suspended in water and given on a spoon. Staff who administer drugs at the health centre will play no further part in the trial. All participants will be kept under observation for 30 minutes after drugs are taken. In case of vomiting, the drug will be re-administrated. At the time of each monthly drug administration, a brief clinical assessment will be carried out. Children who are febrile will be screened for malaria using a rapid antigen test. Children found to have malaria will be treated with Lumefantrine-artemether (CoartemTM, Norvatis Pharma., Basel Switzerland).

*3.8 Treatment*

SP (tablets containing 500 mg sulfadoxine/ 25 mg pyrimethamine) will be given at an approximate dose of 1.25 mg pyrimethamine/25 mg sulfadoxine per kg stat.

Amodiaquine (200 mg base tablets) will be given at an approximate dose of 25 mg/kg over 3 days ( 10mg/kg D1, 10mg/kg D2 and 5mg/g D3).

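### The clinical malaria endpoint has no case definition and an undated window that does not match the dosing months, so it can count malaria before the first dose and one illness twice, and could stop before the third round is followed up

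*Protocol*

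**What the plan says.** - **Endpoint (Protocol 3.12.1).** The clinical efficacy endpoint is "Number of OPD attendances with malaria that meet the case definitions as indicated below during the surveillance period". Sections 3.13 to 3.16 and the references follow, and none of them contains a case definition.
- **Surveillance (3.10).** Under the heading "Morbidity surveillance during the rainy season", the text reads "Passive surveillance for malaria will be maintained throughout the transmission season". No date is given, and neither the start nor the end is linked to a treatment round.
- **Season (3.1).** Transmission is described as "occurring mostly during the short rainy season (July - October". These are the only calendar months the protocol attaches to the season.
- **Dosing (3.7).** "Treatment will be given during the months of September, October and November".
- **Summary.** It opens its account of the three rounds with "During the 2007 malaria transmission season, 1009 children aged 1-5 years will be individually randomized", so there the season includes November.
- **Randomisation (3.6).** It takes place about three weeks ahead of a first dose expected early in September 2007.
- **Other efficacy endpoints (3.12.1).** One is "Prevalence of malaria parasitaemia at the end of the malaria transmission season"; the other is mean haemoglobin at the same undated point. Baseline haemoglobin is available (3.2): "A finger-prick baseline blood sample will be obtained for determination of haemoglobin concentration and thick blood film preparation".

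**The concern.** Efficacy is the only secondary objective (2.2), and the Summary and section 1.2.3 give the reason for the trial: to find combinations that prevent malaria equally well with fewer adverse events. An endpoint that counts malaria arising before any drug is given adds the same background to every arm. That pulls rate ratios towards 1, the direction a reader would take as equal effectiveness.

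Three things leave the count open:

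- Nothing starts it at the first dose. The analysis rule in 3.13 decides which children are included (those who took a first dose), not when their events begin to count.
- The unit is the attendance, so a return visit for the same illness is a second event.
- The end of surveillance and the survey date follow a season that the protocol uses in two senses. One includes the November round and the other does not.

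Survey timing matters for parasite prevalence too. Section 1.2.4 gives piperaquine a half-life of about 17 days, so the difference between arms depends on time since the last dose. Individual randomisation should balance that interval between arms, but without a fixed interval it is unclear what difference is being estimated.

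**Working it through.** **The plan's own figure.** The efficacy endpoints carry none. The stated sample size concerns adverse events: 20% against 10%, two-sided 0.05 and 90% power give 286 per arm with a continuity correction, and 286 × 3 / 0.85 = 1009.4. It reproduces and has no bearing here.

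**Step 1: the calendar.** Inputs are the first dose in early September (3.6), taken as 1 to 7 September; monthly rounds; and randomisation 21 days earlier.

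- Randomisation falls on about 11 to 17 August.
- The third round falls on about 1 to 7 November, after 31 October. A window closing with October would contain no follow-up of it.
- July to October has 123 days, of which 62 to 68 precede the first dose. Arms exist only from randomisation, so about 21 of those days can enter a comparison of arms.

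**Step 2: dilution from pre-dose time.** Assume equal daily malaria rates, no drug effect before the first dose, a first dose on 1 September and a true rate ratio of 0.50 between two arms afterwards. The 0.50 is illustrative; the protocol gives no such figure. With b pre-dose days and d days from the first dose:

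observed ratio = (b + 0.50 × d) / (b + d)

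- Counting to the end of October, d = 30 + 31 = 61: (21 + 30.5) / 82 = 0.63.
- Counting to the end of November, d = 61 + 30 = 91: (21 + 45.5) / 112 = 0.59.
- Counting from the first dose, b = 0: 0.50.

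**Step 3: losing the last month.** With b = 0, the ratio is 0.50 at d = 61 and at d = 91, so a shorter window does not dilute a constant ratio. It does remove 30 / 91 = 33% of the follow-up and, at equal rates, the same share of events. The standard error of the log rate ratio then grows by about √(91/61) = 1.22.

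**Step 4: the case definition.** Section 3.10 stands above the endpoint and is a testing and treatment rule. It contains a 37.5°C threshold, a fever history within 48 hours (for testing; the treatment sentence says only recent), a dipstick, and a thick smear for later confirmation. It does not say whether dipstick or smear decides a case, and it has no rule for repeat visits.

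**Step 5: baseline haemoglobin.** Adjusting for baseline multiplies the effective sample by 1 / (1 − r²): 1 / (1 − 0.16) = 1.19 at r = 0.4, and 1 / (1 − 0.36) = 1.56 at r = 0.6. The correlations are assumed; the protocol gives none.

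**The case against.** The strongest reply is that the protocol plainly means a season that covers the dosing. Section 3.1 says mostly, which describes when transmission is concentrated rather than its limits. The Summary puts all three rounds within the 2007 season, and the 2006 trial, dosed in the same months, had an end-of-year survey (1.2.3). This stands as far as it goes. A reader might infer that the endpoints are bound to miss the third round; the documents do not support that. It is one possible outcome of a literal reading.

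A reader might also count all of July and August as pre-dose time, giving (2 + 2 × 0.50) / 4 = 0.75. That is not supported either: there are no arms before about mid-August, and section 3.10 has staff identify children already in the trial.

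The elements of a case definition are in section 3.10, including the smear. This too stands: what is missing is the definition the endpoint points to, not the data needed to apply one.

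Malaria found by rapid test at a dosing visit (3.7) might be thought to be lost. The protocol does not say so. Dosing takes place at health centres, and whether such cases count is simply unclear.

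Finally, rules for repeat episodes, person-time and covariates often sit in a statistical analysis plan, which is not at hand. That is fair for haemoglobin, where the protocol does not fix an unadjusted comparison. It does not answer the main point: the protocol itself promises the case definition and itself sets attendances as the unit.

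**Conclusion.** The point holds in a limited form. It is certain that the cited case definition is absent, that the surveillance period is undated, and that the only dated season does not match the dosing months. As written, the count could include about 21 days between randomisation and first dose, could count one illness more than once, and could end before the third round is followed up.

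An assumed true ratio of 0.50 would be read as 0.59 to 0.63. This rests on equal daily rates, no effect before dosing, and surveillance that is running from randomisation. If few malaria attendances occur in those three weeks, the dilution is smaller. An October cut-off would add a loss of about one third of the events but no bias of its own under a constant ratio.

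These are secondary endpoints. The primary safety endpoint and the sample size are untouched, so this is something the sponsor should correct rather than a threat to the trial.

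**What to change.** 1. Reconcile the Summary and sections 3.1, 3.7, 3.10 and 3.11 on what the transmission season means. This review takes no position on the dosing schedule.
2. Replace attendances with distinct malaria episodes per child-time, counted from each child's first dose to the final survey, with a stated rule for when a return visit is a new episode.
3. Tie the end of surveillance and the survey to one fixed interval after the third round, the same in all arms.
4. Write the case definition into section 3.12.1 from the elements in 3.10: the 37.5°C threshold or a fever history within 48 hours, with parasites confirmed on the thick film already collected.
5. State whether malaria detected at dosing visits counts. No extra films are required.
6. Compare end-of-season haemoglobin adjusted for the baseline value already measured. This is a gain in efficiency rather than the correction of an error: 1.19 to 1.56 times the effective sample at assumed correlations of 0.4 to 0.6.

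The cost is protocol wording, minor analysis work and possibly a few more weeks of passive surveillance.
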